#### 2.7.2. Secondary Outcomes

**Sociodemographic data**. Attendees will be questioned about their age, revenue, education level, and marital status.

**Height**. It will be assessed using a stadiometer (SECA 225, SECA, Hamburg, Germany). Subjects will stand with feet together, heels, buttocks, and upper back in contact with the scale and head in Frankfort’s plane.

**Bodyweight, fat mass and muscle mass**. Bodyweight shall be measured with a body composition analyser (TANITA MC-780 MA, Tanita Corp., Tokyo, Japan). Estimation of fat and muscle mass will be obtained by electrical bio-impedance using regression formulas.

**Executive function**. As part of the measurement of balance-related tests, subjects will be tested in DT using the nir-HEG headband to observe brain activation. The X-Wiz model will be used for cortical activation measurements in the Fp1 and Fpz/Cz regions of the Nir-HEG/Quantified-EEG/HRV system. The measurements will be based on the multimodal headband and pendant system developed to simultaneously combine the monitoring of Hemoencephalography in the frontal lobe (HEG), 2-channel Electroencephalography (EEG) by theta/Beta ratio, and heart rate (HRV) by the finger sensor [29].

**Regucalcin**. Blood samples will be obtained from the participants by fasting venous puncture in the antecubital vein (10 mL). It will use sterile material by qualified personnel, and these will be evaluated by Western blotting technique. The protocol has been described previously [11].

**Physical fitness**. They will be assessed with the following tests of the Senior Fitness Test Battery [30].

○*The 6–min walking test.* This assessment determines the highest distance each participant can walk for 6 min around a 45.7 m rectangle [31]. This test has been shown to be valid and reliable (*R* = 0.94, CI = 0.90–0.96) [30].○*Lower-limb strength.* The 30-s Chair Stand Test involves of counting the total of times a participant can stand up entirely from a seated position with their back straight and feet parallel to the floor, not including pushing off with their arms inside 30 s [30] (*R* = 0.89, CI = 0.79–0.93).○*Upper-body strength*. Arm Curl test consists of lifting a weight as many times as possible (2.3 kg for women and 3.6 kg for men) by flexing and extending the arm for 30 s (*R* = 0.81, CI = 0.72–0.88). In addition, the handgrip strength test will be executed make use of a digital dynamometer (TKK 5101 Grip-D: Takey, Tokyo, Japan). The participants will perform the test two times (two tries per hand). The greatest value of the two efforts per hand will be taken, and the average of both hands will be treated for the study (ICC = 0.94–0.98) [32].○*Lower-limb Flexibility*. The Chair Sit and Reach Test will be applied (*R* = 0.95, CI = 0.92–0.97). Participants begin from a seated position with one leg stretched. Then, they slowly tilt forward by gliding their hands down the outstretched leg until they touch (or pass) their toes. The centimetres travelled from the toes will be recorded. One try will be performed for every leg and the average of both legs shall be used for analysis [33].○*Upper-limb Flexibility*. The Back-Scratch Test will be performed. Measures the motion range of the shoulder joint through the distance (or overlapping of) the middle fingers behind the back [34] (*R* = 0.96, CI = 0.94–0.98).○*Velocity*. The Brisk Walking Test will be employed. This test involves of determining the time needed by each participant to walk 30 m (ICC = 0.93) [35]. Two repetitions shall be performed with 1 min rest in between. The greatest outcome shall be considered for analysis.○*Agility*. The 8-Foot Up-and-Go Test will be applied. It consists of getting up from a chair, walking 8 steps and going around a cone to get back in the chair as quickly as possible (*R* = 0.95, CI = 0.92–0.97) [30].

**Physical Activity levels**. The International Physical Activity Questionnaire (IPAQ) short version will be applied [36]. This questionnaire provides information on the time spent walking, in vigorous and moderate-intensity activity and sedentary activity. The participants will be instructed to refer to all domains of physical activity.

**Fall Risk**. The 21-item Fall Risk Index (FRI-21) will be applied. It is a questionnaire comprising 21 items. Each item is given a rating of 1 (risk) or 0 (no risk), the amount of all items varies from 0 (minimal risk of falls) to 21 (extreme risk of falls). Elevated scores indicate a higher risk of falls. A cut-off point of 9–10 on the FRI-21 is useful for soon identification of falls risk (sensitivity 0.65) [37,38].

**Fear of falling**. The Falls Efficacy Scale-International (FES-I) will be used to measure fear of falling. It is a questionnaire created and authenticated by the Prevention of Falls Network Europe (ProFaNE). It has come to be a tool with excellent accuracy and authenticity for evaluating fear of falling (ICC = 0.96) in different societies and languages, including Spanish. [39,40,41]. The earliest questionnaire includes 16 items and is scored on a 4-point scale (1 = slightly worried to 4 = very worried). Therefore, the best value that can be obtained is 16 and the worst value is 64.

### 2.8. Statistics

Descriptive statistics and computations will be performed through SPSS (version 25.0; IBM SPSS Inc., Armonk, IL, USA). Data will be presented as means and standard deviation (SD).

Normality and homogeneity of data will be checked applying Kolmogorov–Smirnov and Levene’s tests, respectively. Moreover, an intention-to-treat and a per-protocol analyses will be executed:

**Intention-to-treat analysis**. This analysis will consider all randomly assigned participants in their respective group. Missing data will be input by multiple imputations. Repeated measures ANOVA will be applied to calculate the intervention effects on the different dependent variables, adjusted by age and baseline outcomes. Cohen’s d will be included in results (95% confidence interval) as the effect size. Statistical significance will be computed for the effect of time and the interaction group × time. Alpha level shall be set at *p* ≤ 0.05. Pearson’s bivariate correlations and linear regression will be also computed for analysing the associations between variables.

**Analysis by protocol**. For this analysis, only the volunteers who have completed more than 80% of training sessions will be considered. The same procedures as those indicated for intention-to-treat analysis will be conducted.

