### 2.3. Sample Size Calculation

The number of participants to be included in the studies has been calculated based on the change in plasma regucalcin levels, this actual minimum difference being 38.48 AU [21] with a power of 0.65. Hence, a total of 90 participants are required for the studies to be conducted (45 in the experimental group and 45 in the control group), accepting an alpha risk of 0.05. The common standard deviation in regucalcin is assumed to be 192.4 [11] and a loss-to-follow-up rate of 20% has been estimated.

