### 2.5. Participants

The participants will be recruited in Cáceres, Extremadura (West region of Spain). To be included in the study, participants will meet the following eligibility criteria: (a) age ≥65 years old; (b) not present or suffer any condition or inconvenience that prevents the normal practice of physical activity; (c) complete and sign the consent form; d) not engage in intense physical activity. The exclusion criterion is (a) presenting or suffering from any neurodegenerative pathology. The participants will be informed about the project via a phone call and meeting. All those who pass the inclusion criteria will be included in the study participation, as shown in Figure 1.

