### 2.7. Outcomes and Procedures

Table 3 summarise several measures that will be taken to assess the utility and effectiveness of SSE program in the cognitive and motor domains (Table 3).

Data collection will take place on 2 days, at baseline, 2, 4 and 6 months, in identical order to avoid alterations. On the first day, blood will be drawn and body composition and risk of falls will be assessed, and on the second day, executive function and physical condition will be assessed. One of the researchers will oversee all measurements except for the blood draw (performed by a skilled worker).

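### If age and baseline enter the SPSS repeated-measures ANOVA uncentred, the declared test of time evaluates change at age 0 and baseline 0; group × time is unaffected

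*Protocol article*

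**What the plan says.** All of this is in section 2.8 (Statistics) unless another section is named.

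- Software: "Descriptive statistics and computations will be performed through SPSS", version 25. No SPSS procedure is named.
- Model: "Repeated measures ANOVA will be applied to calculate the intervention effects on the different dependent variables, adjusted by age and baseline outcomes". The text does not say whether the covariates are centred, or whether baseline is also a level of the time factor.
- Declared tests: "Statistical significance will be computed for the effect of time and the interaction group × time". The level is given as "Alpha level shall be set at *p* ≤ 0.05".
- The per-protocol analysis follows the same procedures.
- Section 2.5 sets eligibility at "age ≥65 years old". Section 2.7 puts the assessments at baseline and months 2, 4 and 6. Section 2.3 plans 90 participants, 45 per arm.

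**The concern.** The time effect is one of only two significance tests that section 2.8 declares, and it applies to every outcome in both analysis sets. A reader will take it as the answer to whether the outcome changed over the six months in these participants.

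In the ordinary repeated-measures general linear model with covariates, each within-person contrast is regressed on an intercept, age, baseline and group, and the time line tests whether the intercepts are zero. An intercept is the expected contrast where every covariate equals zero. With raw covariates that is a person aged 0 with a baseline score of 0, far outside an over-65 sample. The printed p-value would then answer a different question. It could miss a real average change, or turn significant when average change is nil.

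**Working it through.** **Inputs from the protocol article.** n = 90; alpha 0.05; assessments at months 0, 2, 4 and 6; age 65 or over; covariates age and baseline. The article gives no figure for the time test, so there is none to reproduce.

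**Assumptions, not in the article.** Age mean 72, SD 5; outcome mean/SD between 1.7 and 3.3; within-person correlation ρ = 0.7; linear change reaching 0.3 SD at month 6 in both arms; covariate × time terms in the model, as in the usual general linear model.

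**1. How far the intercept is extrapolated.** Relative to centred covariates, its standard error grows by about √(1 + (mean age/SD age)² + (outcome mean/SD)²).
- √(1 + (72/5)² + (25/15)²) = √(1 + 207.4 + 2.8) = √211.1 = 14.5.
- With age SD 7: √(1 + 105.8 + 2.8) = 10.5. With age SD 4: √(1 + 324 + 2.8) = 18.1.

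**2. Power, months 2, 4 and 6 as levels.** The true changes are 0.1, 0.2 and 0.3 SD. Their squared deviations from the mean sum to 0.02. Contrast error variance is 1 − ρ = 0.3.
- Centred: noncentrality 90 × 0.02/0.3 = 6.0. On 2 and 172 degrees of freedom (2 × (90 − 4)), power is about 58%.
- Raw: 6.0/211.1 = 0.028, giving about 5%.
- Simulation agrees: 56-58% centred, 5-6% raw.

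**3. Power, baseline also a level.** The changes 0, 0.1, 0.2 and 0.3 SD have squared deviations summing to 0.05.
- Centred: 90 × 0.05/0.3 = 15 on 3 and 258 degrees of freedom, about 91%, ignoring the precision gained from the baseline covariate. Simulation gives 92-93%.
- Raw: about 8-16% in simulation, and 31% in one simulation at mean/SD 3.3.

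The raw figure is not pinned at 5% here because regression to the mean enters. For someone with baseline 0, the model expects a rise of (1 − ρ) × mean even if nothing changes on average: 0.3 × 1.7 = 0.5 SD, or 0.3 × 3.3 = 1.0 SD. Rejection therefore reflects this artefact as well as any real change.

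**4. Rejection when average change is nil.**
- *Change depends on age.* Age 0 lies 72/5 = 14.4 SDs below the mean. A slope of −0.1 or −0.2 SD of change per SD of age implies 1.44 or 2.88 SD of change at age 0. With three levels, the noncentrality is 90 × 2 × (1.44/3)²/0.3/211.1 = 0.65, or 2.6 for the steeper slope. These give about 10% and 28%. Simulation gives 9-10% and 21-26% with three levels, and 22-40% and 65-77% with four. Centred, the rate is about 5-8%. The upper ends are approximate, since they move with the assumed slope and mean/SD ratio.
- *Baseline both covariate and level, no age slope.* The artefact in step 3 alone gives 7-11% in one simulation. Another gives 25% at mean/SD 3.3, with a range of 12-52% for mean/SD from 1 to 6.7. Centred, the rate stays at about 6-7%. The direction is secure; the size is not.
- *Three levels, no age slope.* Raw and centred both reject at about 5-6%.

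**5. Group × time.** Subtracting a constant from a covariate alters only the intercept and leaves the group coefficients unchanged. In simulation the raw and centred group × time p-values differed by no more than about 10⁻¹³.

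**The case against.** The strongest reply is that two unstated choices must both go the wrong way. The article does not say that the covariates stay in raw units, and it names no SPSS procedure. A mixed model without covariate × time terms, or a comparison of times at the covariate means, would avoid the problem. Centring is also a coding detail that an unseen analysis plan might settle. All of that is true, and it makes the point conditional. It does not remove it: the article itself fixes the software, the type of model, the covariates and the test, and the ordinary way of running that combination gives a misleading time line.

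A second reply is that a time effect pooled over both arms answers none of the treatment hypotheses in the Introduction. That also stands, and it limits the severity.

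Three stronger readings are tempting, and the documents do not support them. A reader might infer that the trial's treatment comparison is compromised; it is not, because group × time is unchanged. A reader might infer that the time test will have almost no power for every outcome; that depends on the outcome's mean/SD and on whether baseline is a time level, neither of which is given. A reader might infer that the time p-values will contradict the reported means; that is a possibility under raw entry, not a certainty.

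**Conclusion.** The point holds as a conditional and minor correction. If the declared analysis is run as the usual repeated-measures general linear model with raw covariates, the time test does not address change in the enrolled participants. The loss of power for a real average change is large in every setting examined. The excess of false positives ranges from slight to severe, and requires either change that depends on age or baseline serving as both covariate and time level. All rates rest on assumed age and outcome distributions, correlation and slopes, so they show order of magnitude only. Only the supporting test of time is affected.

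**What to change.** Add one sentence to section 2.8: age and the baseline outcome will be centred at their means over all randomised participants before entry as covariates. Alternatively, state that the time effect will be taken from estimated marginal means at the covariate means and not from the within-subjects time line. Apply the same rule in the intention-to-treat and per-protocol analyses. It would help to say in the same place whether baseline is also a level of the time factor.

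The cost is one sentence and two computed variables in SPSS. No extra data or participants are needed, and the group × time result does not change.

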## Abstract

Background: Age-related changes negatively affect physical fitness, body composition, and executive function and produce a decrease in regucalcin level expression in blood. The square-stepping exercise (SSE) is a balance and lower-limb strength training programme used to prevent falls and stimulate cognitive function in older adults. This project aims to analyse the effects of SSE on executive function, regucalcin expression, fall prevention, body composition, and physical fitness in people over 65 years old. Methods: A randomized controlled trial will be conducted. A total of 90 older people over 65 years old will be recruited and randomly assigned to 2 groups: experimental (*n* = 45) and control (*n* = 45). The experimental group will perform an SSE-based intervention for 6 months (2 times per week), while the control group do not follow any treatment. Results: The main outcome will be balance, but other motor (body mass index, upper- and lower-limb strength, flexibility, and speed-agility) and cognitive variables (executive functions and attention) will be assessed. The expression of regucalcin levels will also be evaluated. Therefore, this project aims to analyse the effect of a 6-month SSE intervention on cognitive and motor competence, physical fitness, regucalcin levels, fall risk, and body composition in older people. If the intervention proves to be effective, it could be implemented in centres, entities, and associations specialized in elderly care.

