Many of the tasks of daily life involve DTs, which are a matter of concern given that because of ageing, older people have problems performing the daily live activities simultaneously. The ability to perform any task may be impaired due to limited attentional resources [15], increased risk of falls [16], loss of independence, and impaired quality of life. Previous studies analysing the effect of DT in older women with fibromyalgia found that gait pattern is affected when an additional cognitive task is added to the primary motor activity; so the walking pattern may be safer and more stable if attention is focused on two simultaneous tasks [17,18]. However, no studies have investigated the impact of DT-based exercise programs on cognitive activity and executive function.

Square stepping exercise (SSE) is a type of physical exercise used in the elderly to reduce the risk of falls [19], but its effects on executive function and regucalcin levels have not been examined. Therefore, this study will analyse the effects of SSE on regucalcin, executive function, physical fitness, balance, fall risk, fear of falling, and body composition in older people. In addition, it will assess the relationship between changes in executive function and regucalcin, physical fitness, balance, fall risk, fear of falling, and body composition in older people.

We hypothesized that (1) SSE will enhance regucalcin levels, executive function, physical fitness, balance, fall risk, fear of falling, and body composition in older people, and (2) changes in executive function and regucalcin will be related to falls, body composition, and physical fitness in older people.

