## 3. Discussion

Internationally, there are more than 300 publications on SSE in high-impact journals, but none have addressed the aspects that this project aims to study. There are many published studies on physical exercise in older people; however, there is no publication that studies the benefits of SSE on executive function, regucalcin, as well as studying the correlations of these changes with the variables of fall prevention, physical condition, and body composition in older people.

The implementation of the SSE has been investigated in adult populations [42,43], as well as in other populations with pathologies such as diabetes mellitus type 2 [44], Parkinson’s [45], and fibromyalgia [23], among others. Therefore, we hypothesize that a 6-month intervention based on SSE will improve the regucalcin levels, executive function, physical fitness, balance, fall risk, fear of falling, and body composition in older people over 65 years old. Furthermore, if the efficacy of this training system is demonstrated as an improvement in the regucalcin levels, it could reduce the risk of developing cancerous tissues, as well as being used as a biomarker in “active” ageing. Similarly, if there are encouraging results in cognitive performance and balance tests, it could indicate an improvement in functionality and performance in activities of daily living. These improvements will provide older people with independence from external aids that will be needed in the after-effects of ageing. Therefore, the implementation of SSE program could be applied by several agents interested in taking advantage of the benefits of this activity.

The SSE training method stands out because it requires neither expensive material nor any specific installation (it can be carried out in open and enclosed spaces) and reports a high applicability due to its adherence and feasibility [46]. Thus, it is a low-cost system standardized by different levels of difficulty (see methodology) that can be implemented at low cost in the public and private health sectors. Therefore, within the public health sector, the implementation of the SSE would be promoted through different services, such as the so-called “Exercise Looks After you” [47]. In the private sector, it is also possible to implement the SSE in associations or centres for the care or entertainment of the elderly.

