## 4. Conclusions

This project will investigate the effectiveness of SSE in people over 65 years of age for 6 months with the aim to analyse the effects of SSE on regucalcin, executive function, physical fitness, balance, fall risk, fear of falling, and body composition. Improvements in these variables will mean a reduced risk of developing cancerous tissues and improved performance in activities of daily living. If this intervention proves to be effective, it could be implemented in those centres, entities, and associations specialized in elderly care.

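### The primary/secondary split has no consequence for inference: about 15 secondary variables are tested at p ≤ 0.05, and the text allows efficacy language on them

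*Protocol article*

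**What the plan says.** **Tiers.** The Abstract singles out one outcome: "The main outcome will be balance, but other motor" and cognitive variables are to be assessed as well. Section 2.7.1 places balance among the primary outcomes, and section 2.7.2 lists the secondary ones.

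**Analysis.** Section 2.8 makes no use of these tiers. "Repeated measures ANOVA will be applied to calculate the intervention effects on the different dependent variables", adjusted for age and baseline. "Statistical significance will be computed for the effect of time and the interaction group × time". One threshold follows: "Alpha level shall be set at *p* ≤ 0.05". For the per-protocol set, "The same procedures as those indicated for intention-to-treat analysis will be conducted".

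**Hypothesis.** Hypothesis 1 in the Introduction reads: "SSE will enhance regucalcin levels, executive function, physical fitness, balance, fall risk, fear of falling, and body composition in older people". Balance is fourth of seven domains and has no precedence.

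**Interpretation.** The Discussion considers what follows "if the efficacy of this training system is demonstrated as an improvement in the regucalcin levels". The Conclusions list all seven domains and continue: "Improvements in these variables will mean a reduced risk of developing cancerous tissues and improved performance in activities of daily living". Implementation is then made conditional on the intervention proving effective, a term that is not defined by reference to balance. Section 2.3 sizes the trial on regucalcin, which 2.7.2 lists as secondary.

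**The concern.** A primary/secondary split protects a trial's conclusion only if the plan says what each tier may support. Here the labels exist, but the significance rule, the hypothesis and the interpretive text all pass over them. A reader who applies 2.8 and hypothesis 1 as written could count any secondary group × time result at p ≤ 0.05 as a confirmed part of the hypothesis.

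At stake is what the trial may claim. With many secondary variables each tested at 0.05, an ineffective programme has a material chance of producing at least one nominally significant benefit. The Discussion and Conclusions attach sizeable claims to such improvements, including a lower risk of cancerous tissue.

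**Working it through.** **Reference figure.** The plan gives no familywise error rate to reproduce. Its only figure on this point is the 0.05 level in 2.8, which is a per-test level.

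**Step 1: count the secondary variables under hypothesis 1 (from 2.7.2).**

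| Domain | Variables | Count |
|---|---|---|
| Body composition | weight, fat mass, muscle mass | 3 |
| Executive function | counted once | 1 |
| Regucalcin | plasma level | 1 |
| Physical fitness | 6-min walk, chair stand, arm curl, handgrip, sit and reach, back scratch, 30-m walk, 8-foot up-and-go | 8 |
| Fall risk | FRI-21 | 1 |
| Fear of falling | FES-I | 1 |
| **Total** | | **15** |

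The physical activity questionnaire (IPAQ) is also in 2.7.2 but lies outside hypothesis 1; adding it gives 16. Analysing executive function as four signals (HEG at two sites, EEG ratio, HRV) would give 18 without IPAQ. The three balance measures, the time effects (which do not compare the arms) and the per-protocol repeat are not counted.

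**Step 2: independent tests, no true effect on any of the 15.**

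- Either direction: 1 − 0.95^15 = 1 − 0.463 = 53.7%.
- Favourable direction only (0.025 per test, taking the tests as two-sided): 1 − 0.975^15 = 1 − 0.684 = 31.6%.
- Expected number of false positives in either direction: 15 × 0.05 = 0.75.

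**Step 3: correlated outcomes.** The documents give no correlations between outcomes, so these are assumed. The model takes test statistics Z_i = √r·U + √(1 − r)·E_i, with U and E_i independent standard normal, and counts a false positive when |Z_i| > 1.96 (either direction) or Z_i > 1.96 (favourable). Probability of at least one among 15, by simulation with 200,000 or more draws (the r = 0 row is exact):

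| Assumed r | Either direction | Favourable only |
|---|---|---|
| 0 | 54% | 32% |
| 0.3 | 46% | 24% |
| 0.5 | 36% | 18% |
| 0.7 | 26% | 13% |
| 0.8 | 20% | 10% |

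**Step 4: sensitivity.**

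- *Form of the test.* Simulating a 2-df group × time F test with 45 per arm and three post-baseline visits (4,000 runs) gives 55%, 37% and 21% at r = 0, 0.5 and 0.8. These are close to the either-direction column. A multi-visit interaction test has no direction, so the favourable-only column is an approximation.
- *Number of tests.* With one test per secondary domain (6 tests), the either-direction figures are 26% (1 − 0.95^6), 21% and 14% at the same correlations. With 16 independent tests they are 56% in either direction and 33% favourable.

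**The case against.** Four points can be made on the other side.

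**The outcomes are already tiered.** This is correct. A reader might infer from 2.8 that the plan has no hierarchy at all, but the Abstract, 2.7.1 and 2.7.2 set one. What is missing is any consequence of it: no order or error control within the secondary tier, and no statement that efficacy claims rest on the primary tier.

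**Multiplicity detail belongs in an analysis plan that is not shown, and unadjusted secondary outcomes are common.** Both statements are fair, and the absence of a correction is not in itself the finding. The finding rests on text that is present: one significance rule for all variables, a hypothesis that sets secondary domains beside balance, and efficacy wording for regucalcin. Unadjusted testing is acceptable when the results are understood as supportive, and the article does not say so.

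**The at-least-one error rate answers a rule that the document does not state.** Hypothesis 1 joins its domains with 'and', so read literally it claims all of them, and 0.05 is never presented as a familywise level. This stands as a limit on the figures: they describe how often chance would supply something to report, not the error rate of a declared decision rule. However, 2.8 tests each variable separately and nowhere requires all of them to succeed.

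**The interpretive passages are conditional.** A reader might infer that roll-out could follow from regucalcin alone, or that one significant secondary could override a null balance result. The documents state neither. The regucalcin sentence leads to cancer risk and biomarker use, not to roll-out; the implementation sentence in the Conclusions stands apart and names no variable. The text leaves such a reading open but does not make it a rule.

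**Conclusion.** The point holds as a defect in stated text: the primary/secondary distinction is drawn, but nothing in the analysis, hypothesis 1 or the interpretation depends on it.

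If the programme affected none of the 15 secondary variables, the chance of at least one false-positive favourable result is about 18% (10% to 32%), and about 36% (20% to 54%) in either direction. These figures assume two-sided tests, which the article does not specify, and equal correlation between outcomes, with 0.5 as the central value and 0.8 and 0 as the ends of the range. The favourable-only figures are the relevant ones for a claim of benefit. They are well above the 5% per-test level but below one half throughout, so it would be wrong to infer that a chance benefit is likely.

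The conclusion does not depend on the exact count or correlation, and it does not imply that all 15 variables need a formal correction.

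**What to change.** - **Section 2.8:** state that the efficacy conclusion rests on the primary balance analysis. State that the outcomes in 2.7.2 are supportive, reported as adjusted between-group differences with 95% confidence intervals, and that an isolated p ≤ 0.05 among them supports no efficacy claim. The age and baseline adjustment, and Cohen's d with its interval, are already planned, so this adds little work.
- **Hypothesis 1, the regucalcin sentence in the Discussion, and the Conclusions:** reword so that 'effective' refers to balance and expected changes in the other domains are described as secondary.
- **Optional:** only if a confirmatory claim on regucalcin or executive function is wanted, test it after a significant balance result, in a fixed order stated in advance.

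These are wording changes and need no extra participants or data. The downside is that an isolated secondary p ≤ 0.05 can no longer be presented as demonstrated efficacy.

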#### 2.6.2. Control Group

Participators will continue with their typical lifestyle and routine. Once the experimental period is completed, the intervention will be offered to the control participants with no charge.

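### Section 2.8 adjusts for baseline but tests only time and group × time; if baseline is a covariate only, a benefit reached by month 2 and held is detected at about the 5% level

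*Protocol article*

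**What the plan says.** The intention-to-treat paragraph of section 2.8 gives the model: "Repeated measures ANOVA will be applied to calculate the intervention effects on the different dependent variables, adjusted by age and baseline outcomes". It then lists what is tested: "Statistical significance will be computed for the effect of time and the interaction group × time". The per-protocol analysis follows the same procedures.

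Section 2.7 sets the visits: "Data collection will take place on 2 days, at baseline, 2, 4 and 6 months". Table 3 repeats these four time points for balance, the primary efficacy outcome, and for nearly every other outcome.

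An effect size is planned: "Cohen’s d will be included in results (95% confidence interval) as the effect size". Which comparison and which visit it refers to is not stated.

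The Introduction states the hypothesis: "SSE will enhance regucalcin levels, executive function, physical fitness, balance, fall risk, fear of falling, and body composition in older people". The comparator is an untreated group (section 2.6.2): "Participators will continue with their typical lifestyle and routine".

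No main effect of group and no between-arm difference at a given visit is listed, and the text does not say whether baseline is a level of the time factor as well as a covariate.

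**The concern.** The hypothesis is that participants given SSE end up better than controls. In a randomised trial that is a between-arm difference, and where it sits in a repeated-measures model depends on how baseline is used.

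- **Baseline as covariate only.** The outcome vector is months 2, 4 and 6. The treatment effect is the group term, or the adjusted difference at a named month. Group × time compares the arm difference at months 2, 4 and 6 with itself. An effect that is present by month 2 and then constant produces no interaction.
- **Baseline as covariate and level.** Group × time now includes the change from baseline, so it does respond to a sustained benefit. But the same measurement stands on both sides of the model, and the test is an omnibus test on 3 degrees of freedom that yields no estimate of the difference at month 6.

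The article names the tested terms but not the model they belong to. On the more natural reading, the listed terms leave out the one that carries the hypothesis, for every outcome including balance. If the right term is chosen only after the data are seen, the choice is open to bias.

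The effect of time averages over both arms, so it says nothing about SSE against control.

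**Working it through.** The plan gives no power figure for this test. The figure in section 2.3 is for regucalcin and is not used here beyond its counts.

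**Inputs from the protocol article**
- 45 per arm with 20% expected loss (section 2.3): 45 × 0.80 = 36 per arm.
- Alpha 0.05 (sections 2.3 and 2.8), taken as two-sided.
- Visits at baseline and months 2, 4 and 6 (section 2.7).

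**Assumptions, not in the article**
- Equal correlation ρ = 0.6 between all visits; SD scaled to 1.
- Two benefit patterns: (i) 0.5 SD at months 2, 4 and 6; (ii) a linear rise of 1/6, 1/3 and 1/2 SD.

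**Baseline as covariate only (levels: months 2, 4, 6)**

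*Group × time.* Noncentrality λ = (n/2) × Σ(δⱼ − δ̄)² / (1 − ρ), where δⱼ is the arm difference at visit j.
- (i) All δⱼ = 0.5, so every δⱼ − δ̄ = 0 and λ = 0. The rejection rate is alpha, 5%, whatever n, ρ or the size of the benefit. Simulation gave 5.3% and 5.6%.
- (ii) δ̄ = 1/3 and Σ = 2 × (1/6)² = 0.0556. λ = 18 × 0.0556 / 0.4 = 2.5. With F on 2 and 136 df, power is about 27%. Simulation gave 26% and 28%.

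*Group term (mean of the three visits, baseline-adjusted).* Residual variance = (1 + 2ρ)/3 − ρ² = 0.7333 − 0.36 = 0.3733. SE = √(2 × 0.3733/36) = 0.144.
- (i) 0.5/0.144 = 3.47; against a critical t of 1.995 on 68 df, power is about 93%. Simulation gave 92.5% and 93.3%.
- (ii) (1/3)/0.144 = 2.31; power is about 63%. Simulation gave 62.6%.

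*Adjusted month-6 contrast.* Residual variance = 1 − ρ² = 0.64. SE = √(2 × 0.64/36) = 0.189. In both patterns the month-6 difference is 0.5, so 0.5/0.189 = 2.65 and power is about 74%. Simulation gave 74–75%.

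**Baseline as covariate and level (four levels), by simulation**
- (i) Group × time: about 74%.
- (ii) Group × time: about 56–59%.

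| Benefit pattern | Group × time, covariate only | Group × time, covariate and level | Group term (unlisted) | Adjusted month-6 contrast (unlisted) |
|---|---|---|---|---|
| Held at 0.5 SD from month 2 | about 5% | about 74% | about 93% | about 74% |
| Linear rise to 0.5 SD | 26–28% | 56–59% | about 63% | 74–75% |

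**Sensitivity.** A separate simulation used 36 and 45 per arm, ρ = 0.5 and 0.7, and 2,000 runs per scenario. With baseline as covariate only and a sustained 0.5 SD, group × time was significant in 4–5% and the group term in 90–99%. For a sustained 0.2 SD (the planning effect in section 2.3: 38.48/192.4 = 0.20) the rates were 5–6% and 24–39%. With baseline also a level and a sustained 0.5 SD, group × time was significant in 64–93%.

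**The case against.** **Baseline may be meant as a visit.** Section 2.7 and Table 3 list it as one of four assessments, and testing group × time is the customary choice when baseline is a level. For a sustained benefit that model gives about 74%, the same as the month-6 contrast. This stands. A reader might infer that the planned test cannot answer the trial's question at all; the text does not support that without the condition that baseline is a covariate only. What remains even then is a moderate loss for a gradual benefit and no month-6 estimate from the test.

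**A condensed article may leave detail to an analysis plan.** True of the definition of Cohen's d or a sphericity correction, and neither is faulted here. But the article does fix the adjustment and the tested terms, and on the usual reading the two do not fit together.

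**The time effect.** A reader might infer that a learning gain shared by both arms would be declared a benefit of SSE. The plan does not say that a time effect alone would be read as efficacy, and group × time stays near 5% under a shared gain however baseline enters. Nor is the time test bound to be significant: with baseline as covariate only, a shared gain complete by month 2 leaves it at about 5%. What stands is only that time pools both arms and is no evidence about SSE, although it is one of just two tests listed for the intervention effects.

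**A mixed model is not required.** Correct. The planned method can produce the needed contrast.

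**Conclusion.** The point holds in conditional form. Section 2.8 leaves the role of baseline open and names no between-arm contrast. If baseline is a covariate only, the listed interaction is blind to a benefit that is reached by month 2 and held: about 5% detection, against about 93% for the group term and 74% for the month-6 contrast. The 5% follows from algebra and depends only on the benefit being constant; the other figures rest on the assumed 0.5 SD, 36 per arm and correlation 0.6. For a benefit that keeps growing, the interaction recovers part of the power (26–28%).

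If baseline is also a level, there is no loss for the sustained pattern and a moderate one for a linear rise (56–59% against 74–75%).

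The time effect is not a treatment comparison, but nothing in the article says it would be used as one.

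**What to change.** Amend the intention-to-treat paragraph of section 2.8 to state that:
- the baseline value and age enter as covariates, and months 2, 4 and 6 are the levels of the time factor;
- the efficacy test is the baseline- and age-adjusted difference between groups at month 6, reported with its 95% CI;
- group × time is supportive, showing whether the difference changes over the visits;
- time effects are reported descriptively.

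The per-protocol analysis inherits the change. A linear mixed model is one way to fit this but is not needed, and multiple imputation can stay as planned. The cost is one paragraph, settled before the data are analysed. No new data, visits or participants are needed.
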